**Methods/Design:**

This is a two-armed single-blinded randomized controlled trial with the target of 300 patients per arm. The setting is eleven community and three academic primary care practices in Metro Detroit. Patients are men and women aged between 50 and 75 years who are not up to date on colorectal cancer screening. ColoDATES Web (intervention arm), a decision aid that incorporates interactive personal risk assessment and preference clarification tools, is compared to a non-interactive website that matches ColoDATES Web in content but does not contain interactive tools (control arm). Primary outcomes are patient uptake of colorectal cancer screening; patient decision quality (knowledge, preference clarification, intent); clinician’s degree of shared decision making; and patient-clinician concordance in the screening test chosen. Secondary outcome incorporates a Structural Equation Modeling approach to understand the mechanism of the causal pathway and test the validity of the proposed conceptual model based on Theory of Planned Behavior. Clinicians and those performing the analysis are blinded to arms.

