## Methods/Design

The study is a two-armed randomized controlled trial with a target of 300 patients per arm. The intervention arm is CW, the web-based interactive DA that contains personal risk assessment and preference clarification tools. The control arm is SW, a non-interactive website that matches CW in design and content except for the omission of interactive risk assessment and preference clarification tools. It should be noted that most US primary care practices do not routinely use web-based DAs. SW in the control arm was created to rigorously assess the effect of the interactive features in CW on the outcomes detailed in the Aims section. The study protocol received ethical approval from the University of Michigan Institutional Review Board (HUM00044733).

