### Randomization of the patients to the intervention arm and the control arm

After completing the patient baseline survey, the computer program will randomize the patients into the intervention arm and the control arm. The randomization will be stratified by practice, gender, and race to ensure there are equal proportions of patients by these factors in both arms.

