### Delivery of the DA intervention (CW/SW)

After randomization, the participating patients will enter the introductory page for CW for those randomized to the intervention arm and SW for those randomized into the Control Arm. In the intervention arm, the patients will access and work through CW. On entering CW, the patient will be guided to Overview, then Personal Risk Assessment, where they will interactively answer questions about their personal and family health history. There will be immediate feedback on whether they are ‘Average Risk’, ‘Increased Risk’, or ‘Unknown Risk’ (this occurs if the patient, who is otherwise average risk, answers ‘I don’t know’ to any of the questions in the Personal Risk Assessment). Next, the patients will be guided to access the Comparison Table providing information on CRCS tests (see Figure 2) and a Preference Clarification Tool from which they may select the three most important issues of a CRCS test (see Figure 3). The test most closely matching the three selected issues will be provided. The patients may work on the tool for as long as they wish. Once they select the matched test, a Feedback Page reviewing their test of choice in the context of their risk will be provided: ‘Average Risk’, ‘Increased Risk’, or ‘Unknown Risk’. The combination of patient risk profile and preference will help the patients to understand the details of CRCS, how each test correlates with their preference, their risk for CRC, and how their preference may or may not match the recommended test based on their risk. They will be given a final opportunity to select a CRCS test based on their risk and preferences. Once they submit their choice, a Summary Page will appear that shows them: their risk, their three most important issues, CRCS test based on the three issues, and the test they ultimately selected. Participating patients in both intervention and control arms will undergo the intervention in a private room. For patients needing help using the computer, the research assistant will provide this support but will not counsel them on CRCS. These provisions will ensure privacy, standardization, and inclusion of patients without Internet access and low computer literacy and skills.

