### Aim 1: to measure the impact of CW on patient uptake of CRCS

H-1: patients in the intervention arm will have higher rates of CRCS adherence at the six month follow-up than those in the control arm.

The study arms will be compared to assure that randomization achieved similar study population with respect to age, gender, race, previous CRCS, practice site, and data completion. Medically documented completion of CRCS will be compared between the intervention arm and the control arm by means of a chi-square test (unadjusted analysis) and a logistic regression adjusting for potential predictors at baseline. The regression analysis will be performed with data at the patient level with completing CRCS (yes/no) as the outcome measure and the arm assignment (intervention arm versus control arm) as the main covariate of interest. The practice indicator will further be included as a covariate in order to account for the variation between practices. The clustering effect due to clinician will be accounted for by using a generalized estimating equations approach. Personal patient-level background information (for example, age, race, education, marital status, smoking, health status, health insurance) from the patient baseline survey will be considered for inclusion in the regression model. The model will further be adjusted for information about the patient’s past experience with the CRCS procedures and the baseline level of patient determinants (for example, knowledge, attitude, subjective norm, self-efficacy) and intent. We will also adjust for OPTION score and pertinent clinician-level covariates such as the clinician’s communication style from the clinician survey. In order to understand whether there is any difference in the completion of CRCS rates between groups of patients who (a) complete the risk assessment tool only, (b) complete the preference clarification tool only, (c) complete both, and (d) complete neither, we will use a four level factor indicating this group membership as an independent variable in the regression model.

The contribution of a specific group of covariates will be measured by means of increase in generalized R-square defined as:$$R^{2}\left(\mathrm{increase}\right)=\exp\left(-L_{1}^{2}/n\right)-\exp\left(-L_{2}^{2}/n\right)$$where $L_{1}^{2},L_{2}^{2}$ are the likelihood ratio statistics of the smaller and larger models, respectively.

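### The four-level tool-completion factor in the Aim 1 regression is mixed with randomised arm, because every control patient falls in the *neither* level; it should be confined to the CW arm and labelled non-randomised

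*Protocol article*

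**What the plan says.** Protocol article, Analysis, Aim 1: the patient-level logistic regression for completed screening takes "the arm assignment (intervention arm versus control arm) as the main covariate of interest". The same paragraph then asks whether screening differs between patients who "a) complete the risk assessment tool only, (b) complete the preference clarification tool only, (c) complete both, and (d) complete neither", and answers that "we will use a four level factor indicating this group membership as an independent variable in the regression model". It does not limit this to the CW arm, does not say whether arm stays in the model, and does not call the analysis exploratory.

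Three other sections bear on it:

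- Methods/Design: SW "matches CW in design and content except for the omission of interactive risk assessment and preference clarification tools".
- Randomization of the patients: "After completing the patient baseline survey, the computer program will randomize the patients into the intervention arm and the control arm". Allocation therefore comes before any tool is opened.
- Delivery of the DA intervention: CW leads patients to the risk assessment and then to the preference tool, and "The patients may work on the tool for as long as they wish". How much of a tool is used is partly the patient's choice.

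Alternative strategies records that a 2 × 2 design and a three-arm design were considered and rejected. The tools were therefore never randomised separately.

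**The concern.** A factor for tools completed looks like a way to learn which tool matters. In this design it cannot do that cleanly, for two reasons.

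First, it is tied to arm by construction. SW patients cannot complete a tool they were never shown, so they all share one level with the CW patients who completed nothing. Any contrast against that level is largely a contrast against the control arm.

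Second, within CW the levels are formed by behaviour after randomisation. Patients already inclined to be screened may be the ones who finish the tools.

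At stake is the reading of a secondary result (a difference between levels taken as a tool effect) and, if the factor and arm are put in one model, the meaning of the arm coefficient in that model.

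**Working it through.** **1. The plan's own figure.** Inputs from Sample size and power: 24% versus 39%, two-sided 5%, 90% power, continuity-corrected chi-square. With d = 0.15 and mean rate 0.315:

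n = [1.960·√(2·0.315·0.685) + 1.282·√(0.24·0.76 + 0.39·0.61)]² / 0.15² ≈ 199.5, which is 200 per arm uncorrected.

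With correction: n/4·[1 + √(1 + 4/(n·d))]² ≈ 212.6, so 213 per arm. This matches the plan. The point does not rest on an arithmetic error, and the plan gives no figure for the four-level factor.

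**2. Who is in the *neither* level.** With 300 SW patients and a share s of 300 CW patients completing neither tool, the SW share of the level is 300/(300 + 300s). For s = 2%, 10% and 30% (assumed; the article gives no rates) this is 98%, 91% and 77%.

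**3. Arm left out.** Take the planned 24% and 39%, no difference by tool use within CW, and s = 10% (30 CW patients). The *neither* level has rate (300·0.24 + 30·0.39)/330 = 83.7/330 = 25.4%, odds 0.340. The *both* level has rate 39%, odds 0.639. The odds ratio (OR) is 0.639/0.340 = 1.88, although tool use makes no difference within CW. A simulation (400 trials, 300 per arm, assumed completion of about 73% and 62% for the two tools) gave the same median OR of 1.88, and the factor was significant at 5% in 83% of trials. The factor is reporting the arm effect.

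**4. Arm kept.** Write logit P = β₀ + β_A·arm + β₁·(risk only) + β₂·(preference only) + β₃·(both).

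- SW patients have β₀ and CW *neither* patients have β₀ + β_A. So β_A compares CW non-completers with SW, which is not CW versus SW as randomised.
- With s = 10% it rests on 30 CW patients. Even with no selection, its standard error is √[1/(30·0.39·0.61) + 1/(300·0.24·0.76)] = √(0.140 + 0.018) = 0.40, against √[1/(300·0.39·0.61) + 1/(300·0.24·0.76)] = √(0.014 + 0.018) = 0.18 for the full arms.
- If no CW patient is in *neither*, arm equals the sum of the three level indicators. The design matrix then has rank 4 with 5 columns, and arm and factor cannot both be estimated.

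**5. Motivation.** Simulated trials with no effect of CW, 300 per arm and a 24% rate. Assumed: motivation correlates 0.5 with completing the tools and adds 0.7 to the log-odds of screening per SD. Entries are false-positive rates for *both* versus *neither* at nominal 5%, over 60% to 80% completion of both tools:

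| Model | Arm out | Arm in |
|---|---|---|
| No baseline adjustment | about 13% to 28% | about 31% to 43% |
| Adjusted for a baseline measure capturing 50% to 70% of motivation (assumed) | about 7% to 11% | about 7% to 14% |

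The unadjusted excess is smaller at high completion: 9% (arm out) and 15% (arm in) at 90%. In the unadjusted runs with arm kept, the arm OR fell to 0.71 and 0.66 at 60% and 70% completion although CW had no effect.

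**The case against.** The strongest reply is that H-1 is untouched. It is tested by an unadjusted chi-square test, on which the sample size rests, and by a regression described as adjusting for baseline predictors. Tool completion is not a baseline variable, and it is introduced for a separate question, so a supplementary analysis is a natural reading. This stands. A reader might infer that the primary result is compromised. The article does not support that: the chi-square test and an arm-only regression are unaffected, and the arm coefficient changes meaning only where the factor and arm share a model.

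The second reply is that Aim 1 plans adjustment for past screening experience, baseline determinants and intent, which are measures of motivation. This also stands in large part. The unadjusted false-positive rates describe a model the plan does not propose, and the adjusted rates are several times smaller at low completion. Adjustment does not remove the mixing with arm, though, because that comes from how the levels are defined.

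Third, completion may be high, since patients are guided through the tools in a private room with computer help available. That reduces the selection bias but brings the model closer to the case where arm and factor are inseparable.

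A reader might also infer that the factor breaks analyst blinding, given "Clinicians and those performing the analysis are blinded to arms". Levels (a) to (c) do identify CW patients, but CW and SW data retrieval protocol and Data collection instruments already provide for retrieving usage data to check tool use in CW. Dropping the factor would not by itself secure blinding, so this is secondary.

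**Conclusion.** The concern holds for the factor as written, and the change should be made. The firm part is structural and needs no assumption about motivation: levels (a) to (c) exist only in CW, level (d) pools all SW patients with CW non-completers, and neither leaving arm out nor keeping it gives a usable two-arm model.

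The size of the arm-out problem (OR 1.88, significant in 83% of trials) rests on the plan's 24% and 39% and on assumed tool completion. The motivation bias is real but conditional: about 7% to 14% false positives under the planned adjustment if it captures 50% to 70% of motivation. The article gives neither completion rates nor motivation effects, so these are ranges under assumptions and not predictions.

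**What to change.** State in Aim 1 that the tool-completion factor is not entered in the H-1 model or in any model that includes SW patients. Analyse tool completion within the CW arm only, adjusted for baseline determinants and intent, and label it exploratory and non-randomised.

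The cost is wording. No data, patients or power for H-1 are lost, and the usage data and manipulation-check questions remain available. The trial gives up a causal claim about individual tools, which the two-arm design could not support in any case.

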### Variable selection

In view of a potentially large number of candidates for inclusion as covariates, we will use a simple screening method as follows. Each potential covariate will be investigated for *confounding* effect by running a preliminary screening analysis with and without the covariate in the model along with the study arm and retaining the ones for the final logistic regression model, which either: (a) have a significant effect on the outcome; or (b) change the co-efficient of the study arm variable by more than 5%. *Moderating* effect of a potential covariate × will be investigated by including a study arm × interaction term in the model.

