### Aim 2: to evaluate the impact of CW on patient determinants, patient preference, and patient intention before the patient-clinician encounter

H2-1: patients in the intervention arm will show greater improvement from baseline in patient determinants (knowledge, attitude, subjective norm, perceived self-efficacy) compared to the control arm after the web intervention and before the patient-clinician encounter.

H2-2: patients in the intervention arm will be more likely to have a preference for a particular CRCS test option than those in the control arm after the web intervention and before the patient-clinician encounter.

H2-3: patients in the intervention arm will have higher intention to undergo CRCS than those in the control arm after the web intervention and before the patient-clinician encounter.

We will test Hypothesis H2*-*1 by means of linear regression analysis. We will use a separate model for each determinant. In each case, the post-web aggregated score for the scale under consideration will be used as the dependent variable. As before, the arm assignment (intervention arm versus control arm) will be the primary independent factor. The model will be further adjusted for the baseline score of the corresponding determinant and the patient-level demographic information.

Hypothesis H2*-*2 will be investigated by a logistic regression analysis with a dichotomous outcome indicating whether or not the subject has a clear preference for a CRCS test option in the patient post-web survey. This analysis will be undertaken only for the subgroup of subjects in either arm who did not have a clear preference at baseline. The demographic information will be used as independent variables as before.

Hypothesis H2*-*3 will be investigated using a model similar to that for Hypothesis H2*-*1, but the patient intention post-web will replace the patient determinants post-web as outcome, and the patient intention score at baseline will replace the patient determinants at baseline as independent variable.

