### Randomization strategy

Randomizing at the patient level facilitates recruitment and makes the study more feasible to complete in the given timeframe. Also, patient level randomization helps in balancing across potential patient level confounders and increases statistical power to detect an intervention effect. Clinicians will be blinded to the randomization. We considered randomization at the level of the practice. Such a design would be necessary if there was a risk of contamination between the intervention arm and the control arm within a practice if randomization occurred at the patient level. This is not a concern in our proposed project for two reasons. First, patients in the intervention arm will not have access to SW, and patients in the control arm will not have access to CW. Second, clinicians will not have the resources (time, expertise, desire) to replicate the CW experience. The clinicians could give an information brochure that replicates the SW content, but this would only be additive at best to either CW in the intervention arm or SW in the control arm.

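### The adjusted arm comparisons do not guarantee the randomisation strata: gender and race can be screened out of the Aim 1 model, and the Aim 2 models do not name practice; the cost is small and conservative

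*Protocol article*

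**What the plan says.** All references are to the protocol article.

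- **Randomization of the patients to the intervention arm and the control arm:** "The randomization will be stratified by practice, gender, and race". The unit is the patient (Randomization strategy: "Randomizing at the patient level facilitates recruitment").
- **Analysis, Aim 1:** an unadjusted chi-square test and an adjusted logistic regression. In the regression practice is assured: "The practice indicator will further be included as a covariate in order to account for the variation between practices". Clinicians are handled separately: "The clustering effect due to clinician will be accounted for by using a generalized estimating equations approach". Race appears in a list of examples that "will be considered for inclusion in the regression model". Gender is not in that list.
- **Variable selection:** each potential covariate is tried alongside study arm. It goes into the final logistic model if it is significantly related to the outcome, or if it would "change the co-efficient of the study arm variable by more than 5" per cent. Nothing exempts the stratification factors.
- **Analysis, Aim 2:** the linear models are "adjusted for the baseline score of the corresponding determinant and the patient-level demographic information". The H2-2 logistic model uses demographics. Practice is named in neither.
- **Analysis, Aim 3:** the text refers back to the whole Aim 1 strategy. Aim 2 has no such reference.

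**The concern.** An analysis should reflect the restrictions placed on the randomisation. Here two of the three stratification factors can leave the Aim 1 regression, and the third is not named in Aim 2.

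The screening rule also suits a randomised comparison poorly. Confounding of the arm effect at baseline can arise only by chance, and the stratified factors are the ones least exposed to it. A covariate can move the arm coefficient in a logistic model merely because it is prognostic, even with perfect balance. When the arm coefficient is near zero, 5% of it is almost nothing, so chance imbalance in an irrelevant variable is enough to pass. The rule therefore tends to drop design factors and admit noise, and it chooses the adjusted estimate partly by how far that estimate moves.

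At stake are a little precision and the standing of the adjusted result as a prespecified analysis.

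**Working it through.** **1. The plan's own figures (Sample size and power).** Inputs: 24% against 39%, two-sided 5%, 90% power, continuity correction.

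- Uncorrected: n = [1.960·√(2·0.315·0.685) + 1.2816·√(0.24·0.76 + 0.39·0.61)]² / 0.15² = 199.4, so 200.
- Corrected: (199.4/4)·[1 + √(1 + 4/(199.4·0.15))]² = 212.6, so 213 per arm, as stated.
- Standardised difference 0.23 with 300 per arm: SE = √(2/300) = 0.0816; power = Φ(0.23/0.0816 − 1.960) = 80.4%, as stated.

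Nothing below changes the required sample size.

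**2. Practice omitted from the Aim 2 linear models.** Let ρ be the share of residual variance explained by practice. The article gives no value, so a range is assumed. With practice balanced by design, the true SE is 0.0816·√(1 − ρ), while the model without practice reports about 0.0816. The ratio is 1/√(1 − ρ). Actual alpha is 2[1 − Φ(1.960/√(1 − ρ))].

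| ρ | Reported SE too large by | Actual alpha | Power at 0.23, practice omitted | Power at 0.23, practice included |
|---|---|---|---|---|
| 0.02 | 1.0% | 0.048 | 80.7% | 81.2% |
| 0.05 | 2.6% | 0.044 | 81.0% | 82.4% |
| 0.10 | 5.4% | 0.039 | 81.7% | 84.4% |

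A simulation agrees. It used 1,500 runs per scenario, 597 patients, 14 practices sized by the clinician counts in Table 1, and permuted blocks within practice × gender × race. Type I error without practice was 0.051, 0.042 and 0.035 at the same three values.

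**3. Gender or race omitted from Aim 1.** The outcome variance explained is about β²·q(1 − q)·p(1 − p). Here p = 0.315 (midpoint of 24% and 39%) and q = 0.50 for gender (assumed) or 0.25 for African American patients (Patient population and eligibility criteria). The log odds ratio β is assumed.

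- Race, β = 0.2: 0.04·0.1875·0.2158 = 0.2%; mismatch 0.1%.
- Gender, β = 0.5: 0.25·0.25·0.2158 = 1.3%; mismatch 1/√(1 − 0.013) − 1 = 0.7%, alpha about 0.0485.

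In a logistic model the main effect of leaving out a balanced prognostic factor is a slightly attenuated arm coefficient.

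**4. How the screen behaves.** The simulation used stratified allocation, arm log odds ratio 0 or 0.4, and practice forced into the final model. Generalised estimating equations were not used.

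| Log odds ratio for gender / race | Gender dropped | Race dropped |
|---|---|---|
| 0 / 0 | 87–95% | 84–94% |
| 0.2 / 0.3 | 74–81% | 63–69% |
| 0.5 / 0.5 | 27–28% | 33–36% |

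With no covariate effect and no arm effect, gender was kept in 100 − 87.3 = 12.7% of trials and race in 100 − 84.4 = 15.6%. The significance rule alone would keep about 5%, so the 5% change rule adds roughly 8 to 11 points. At arm log odds ratio 0.4 it adds about 1 point (5.5% and 6.4% kept). In a separate simulation an unstratified pure-noise variable was kept in about 36% of trials with no arm effect and 17% at arm log odds ratio 0.3.

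**5. Error rates after screening.** Type I error was 0.047–0.059 with the screen and 0.050–0.063 with all candidates fixed. Power at arm log odds ratio 0.4 was 58.4–58.5% with the screen and 57.8–58.4% fixed. Screening neither inflates error visibly nor buys power.

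**6. Movement without confounding.** For a balanced covariate with log odds ratio β per SD, the arm coefficient grows by about √(1 + 0.346β²). At β = 0.7 this is √1.170 = 1.08, an 8% shift. At β = 0.3 it is 1.015. The 5% threshold is reached at β = √((1.05² − 1)/0.346) = 0.54.

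**The case against.** The strongest reply is that little harm follows.

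- **The chi-square test is fully specified.** It is listed under Aim 1, it is the basis of the sample size, and no screening touches it. This stands. A reader might infer that the main Aim 1 result is unknown until the outcome data are seen. The article does not support that; the dependence is confined to the adjusted regression. The article does not say which of the two is primary, and the chi-square test itself uses none of the strata.
- **No false-positive problem.** A reader might infer inflated type I error or standard errors that are too small. The calculations show neither: the mismatch is conservative, and for gender and race it is close to nil. The strata most often dropped are those that matter least.
- **Non-collapsibility rarely decides anything.** A covariate strong enough to move the coefficient by 5% in this way (0.54 per SD) would almost surely pass the significance rule in 600 patients. This stands; the practical weakness of the 5% rule is chance imbalance when the arm effect is small.
- **Analysts are blinded to arm (Abstract).** This limits motivated selection, but a rule applied blind still ties the model to the outcome data.
- **Much is already planned.** Aim 1 says the model will be adjusted for past screening experience, baseline determinants and intention, and the H2-1 and H2-3 models carry the baseline score. A reader might also infer that Aim 2 omits gender and race; its demographic adjustment plausibly covers both, so the gap there is practice.
- **Forcing in practice has a cost.** Five of the 14 practices in Table 1 have one clinician. With 49 clinicians in all, 600/49 is about 12 patients for each, if recruitment follows clinician counts. The H2-2 model uses only patients without a clear baseline preference, so sparse cells are likely. This stands and shapes the fix.

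**Conclusion.** The point holds as a modest one. The stated rule lets two stratification factors fall out of the Aim 1 adjusted model, uses a 5% change criterion that is not a valid test of confounding under randomisation, and makes the adjusted arm estimate depend on the trial's own outcome data. The Aim 2 models as written do not name practice. In the linear models this makes standard errors about 1.0% to 5.4% too large if practice explains 2% to 10% of residual variance, and costs about 0.5 to 2.7 points of power at a standardised difference of 0.23. That range is an assumption. For gender and race the mismatch is about 0.1% to 0.7% at assumed log odds ratios of 0.2 to 0.5. No conclusion about invalid error control follows. The gain from a change is an adjusted model known in advance, plus a little precision.

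**What to change.** In the adjusted arm comparisons of Aims 1 to 3:

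1. Always include practice, gender and race, coded as used in the randomisation.
2. State in advance how small practices are pooled where cells are sparse. The five one-clinician practices are the obvious candidates, and the H2-2 subgroup model needs the rule most.
3. Fix the baseline covariates already planned: age, past screening experience, baseline determinants and intention, and the baseline value of the outcome where one exists. Shared decision making has none.
4. Restrict the screening rule to exploratory or labelled sensitivity analysis.

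The cost is wording, a few extra model terms and one pooling rule. Sample size and data collection do not change, because the baseline survey is completed before randomisation. The article reports 339 of 600 patients recruited and analysis starting in April 2015, so the change can be made before outcomes are analysed.
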